### Discontinuation of Treatment or Removal From the Study

A participant can be discontinued from ongoing drug treatment upon the occurrence of AEs related or unrelated to the drug treatment. If a participant fails to return for 1 or more follow-up appointments, data may still be collected upon attendance of the remaining appointments for up to 1 year after the last date of drug administration.

### Interventional Methods

Step 1: twice-daily administration of 200 mg of dovramilast to be taken with fatty food. The treatment will be for 10 days, with a rollover for a total of 28 days if safety and efficacy demonstrate benefit by day 10 for the patient. Step 2: twice-daily administration of 200 mg of dovramilast in patients to be taken with fatty food for 12 weeks, with additional 12-week treatment cycles (week 48) depending on individual clinical needs.

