#### Step 1: Evaluation of the Immediate Effects

To evaluate the immediate effects of dovramilast, 10 male participants with moderate to severe, new, or recurrent ENL will receive an initial 10 days of treatment with 200 mg of dovramilast twice daily. The physician has the discretion to determine whether individual prospective participants with severe neuropathy or other severe symptoms should be enrolled. Participants will be males aged 18 to 65 years and weigh greater than or equal to 40 kg. The initial 28-day safety evaluation (step 1) was limited to male participants as a precautionary measure to minimize potential reproductive and pregnancy-related risks during early exposure to dovramilast in patients with ENL. Although dovramilast has demonstrated an acceptable safety profile in previous phase 1 and phase 2 studies in other disease settings, comprehensive reproductive safety data in ENL populations are limited. Restricting early enrollment to males allowed close monitoring of short-term safety and tolerability before broader inclusion. Upon confirmation of acceptable safety by the Data Safety Monitoring Board (DSMB), enrollment was expanded in step 2 to include both male and female participants, with appropriate exclusion of pregnant or breastfeeding women. Safety and efficacy monitoring assessments will be performed by DSMB representative clinicians during the initial 7- to 10-day treatment period. If assessments during the 10-day initial treatment trial indicate poor safety or efficacy, participants may be removed from the treatment no later than day 10. If assessments during the 10-day initial treatment period indicate that the drug is well tolerated and the participant’s ENL symptoms are responding, the treatment will be continued until day 28. If the drug treatment is not well tolerated, or if assessments for efficacy fail to demonstrate ENL symptom relief, participants may be removed from the treatment.

Upon review of the 10- and 28-day assessments, the DSMB will recommend that another cohort of 40 participants be enrolled for up to 12 months of treatment (step 2).

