#### Step 2: Evaluation of the Long-Term Effects

Participants will be either male or female, aged 18 to 65 years, with a new or newly recurrent ENL episode and will receive 200 mg of dovramilast twice daily. Male weights will be aligned with step 1 requirements (≥40 kg), whereas females should weigh at least 35 kg.

In a subset of participants during step 2, pharmacokinetic assessments of drug levels in the blood will be performed using plasma collected at appropriate times on day 1 and day 10 (predose and 3 hours postdose) after dovramilast treatment.

As in step 1, participants will be enrolled for an initial 7 to 10 days of treatment. If patients tolerate the drug well and respond, they will continue to receive dovramilast for 12 weeks.

Every 12 weeks of treatment, dovramilast will be discontinued to determine if ENL symptoms recur or if the ENL episode has fully recovered. If symptoms recur after 28 days within the 1-year follow-up period, dovramilast will be administered again for another 12 weeks, as indicated by individual patient needs, for up to 1 year of total dovramilast treatment duration (12 wk × 4=48 wk total). Based on individual patient clinical needs, this discontinuation test will be repeated at 6 and 9 months for a total treatment period of up to 52 weeks. While clinical care may occur more frequently as indicated by individual ENL symptoms, participants will be evaluated on days 10 and 28 and monthly during treatment, and monthly for 1 year after discontinuation of the drug (final visit).

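### Step 2's early continuation check is a condition in one section and missing from the dosing section, and it can fall before the day-10 primary assessment with no rule for those already stopped

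*Protocol article*

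**What the plan says.** All references are to the protocol article.

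- **Step 2: Evaluation of the Long-Term Effects** sets an early check: "As in step 1, participants will be enrolled for an initial 7 to 10 days of treatment". It continues: "If patients tolerate the drug well and respond, they will continue to receive dovramilast for 12 weeks". Its visit schedule says "participants will be evaluated on days 10 and 28 and monthly during treatment", then monthly for a year once the drug is stopped. The pharmacokinetic subset has "plasma collected at appropriate times on day 1 and day 10 (predose and 3 hours postdose) after dovramilast treatment".
- **Interventional Methods** says of step 1: "The treatment will be for 10 days, with a rollover for a total of 28 days if safety and efficacy demonstrate benefit by day 10". Of step 2 it says "twice-daily administration of 200 mg of dovramilast in patients to be taken with fatty food for 12 weeks", with further 12-week cycles according to clinical need and no early condition.
- **Step 1: Evaluation of the Immediate Effects**, which step 2 is said to follow, places the check in a window: "Safety and efficacy monitoring assessments will be performed by DSMB representative clinicians during the initial 7- to 10-day treatment period". If safety or efficacy is poor, "participants may be removed from the treatment no later than day 10".
- **Discontinuation of Treatment or Removal From the Study** gives adverse events as the ground for stopping drug and does not mention non-response.
- **Primary and Secondary Outcomes** defines the primary outcome as complete clinical response by day 10.
- **Data Analysis** includes everyone given one dose or more, whatever their treatment duration, and rules out imputation.

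**The concern.** Two things are left open.

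The first is who receives 12 weeks of drug. A site working from the Step 2 section would apply a check on tolerability and response. A site working from Interventional Methods would find a check for step 1 and none for step 2. This matters because the study design overview withholds standard prednisolone and thalidomide regimens during study drug treatment. The sections therefore differ on whether a non-responder continues on dovramilast without those regimens.

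The second is what happens to the primary outcome in someone stopped before day 10. The decision window opens at day 7, but the response is measured at day 10. If those stopped early are not assessed, the people missing from the primary proportion are mostly non-responders, and the available-data rule drops them.

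**Working it through.** The article gives no power calculation and no assumed response rate, so there is no planned figure to reproduce. The check is a comparison of sections followed by a small illustration.

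**1. The continuation rule for step 2**

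| Section | Early condition for step 2? | Nature |
|---|---|---|
| Step 2 section | Yes, after 7 to 10 days | Continuation depends on tolerability and response |
| Step 1 section (which step 2 follows) | By reference | Removal is permitted, not required |
| Interventional Methods | None stated; stated for step 1 just before | 12 weeks |
| Discontinuation section | Non-response not named | Adverse events only |

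Stopping for non-response in step 2 therefore rests on the Step 2 section and its reference back to step 1. At two doses a day, the exposure at stake is 7 × 2 = 14 doses (stopped at day 7) or 10 × 2 = 20 (day 10), against 84 × 2 = 168 over 12 weeks.

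**2. The timing**

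The check can fall on days 7 to 10. The visit, the second pharmacokinetic sample and the primary outcome are at day 10. The Step 2 schedule lists days 10 and 28 as visits during treatment and then gives a monthly schedule after discontinuation. Read literally, a participant stopped on day 7 moves to the monthly schedule and need not be seen on day 10. Safety and Efficacy does not settle this, because its efficacy assessment days are day 0, day 28 and 1 year after cessation. A participant who is seen on day 10 after stopping is off drug, and the restriction on standard ENL treatment no longer applies, so the finding may reflect other therapy.

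**3. Effect on the primary proportion**

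Assumptions, none of them from the article except the maximum of 40: N = 40 in step 2; r responders; m participants stopped early, all non-responders, with no day-10 data. The available-data estimate is r/(40 − m). Intervals are exact (Clopper-Pearson) 95%.

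| r | m = 0 | m = 2 | m = 4 | m = 8 |
|---|---|---|---|---|
| 16 | 40.0% (24.9 to 56.7) | 42.1% (26.3 to 59.2) | 44.4% (27.9 to 61.9) | 50.0% (31.9 to 68.1) |
| 20 | 50.0% (33.8 to 66.2) | 52.6% (35.8 to 69.0) | 55.6% (38.1 to 72.1) | 62.5% (43.7 to 78.9) |
| 28 | 70.0% (53.5 to 83.4) | 73.7% (56.9 to 86.6) | 77.8% (60.8 to 89.9) | 87.5% (71.0 to 96.5) |

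The inflation factor is 40/(40 − m): 40/36 = 1.11 for m = 4 and 40/32 = 1.25 for m = 8. If those stopped are assessed at day 10, or counted as non-responders, the m = 0 column applies and there is no shift.

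**The case against.** The best defence is that this is an omission in a condensed article. The Step 2 section is the dedicated text and is explicit. Interventional Methods is a short regimen summary and never says that step 2 participants receive 12 weeks regardless of response. Figure 3, captioned as covering the treatment decision process, is not available here and may show the check. This limits the severity. It does not remove the mismatch, because the same short summary does give the condition for step 1, and the discontinuation section is silent on non-response.

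It is also fair to say that no section states that day-10 data will be lost. The outcome is response by day 10, and every dosed participant belongs to the analysis. That stands: the loss is a possible consequence. But inclusion in the analysis set does not supply a missing value when imputation is ruled out.

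A reader might go further and infer that the check makes the trial understate intolerance for its primary safety question. The documents do not support this. The safety analysis covers everyone dosed and includes the frequency of interruptions, reductions and discontinuations, so a participant stopped on day 7 for intolerance is counted. Nor would 12-week data come from everyone dosed without the check, since adverse events can end treatment under either version. Any figure for lost precision at week 12 would rest on an assumed pass rate.

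A reader might also see a serious loss of pharmacokinetic data. Only a subset is sampled, and anyone who stops before day 10 lacks the on-treatment day-10 sample whichever section is followed.

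**Conclusion.** The concern holds in a limited form. The sections disagree on whether step 2 has an early continuation check, and they leave unclear whether removal is mandatory or discretionary and on which day it is decided. No view is taken here on which rule is right.

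Because the check can precede day 10, the primary proportion is exposed to upward bias. In the illustration with 20 responders it is 5.6 percentage points if 4 stopped non-responders lack data (55.6 − 50.0) and 12.5 points if 8 do (62.5 − 50.0). These sizes rest on assumed counts, on all those stopped being non-responders, and on their having no day-10 assessment; without that last condition the bias is zero.

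The safety consequence is one of description only: if the check is kept, results at week 12 and later come from those who passed it. Recruitment was unfinished in April 2026, with 15 participants in total, so clarification can still take effect.

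**What to change.** 1. Reconcile the Step 1, Step 2, Interventional Methods and discontinuation sections into one rule stating whether the step 2 check applies, whether removal is mandatory or discretionary, and on which day it is decided. The study team decides the clinical content.
2. For anyone stopped before day 10, require the full response assessment at the decision visit and keep the day-10 visit.
3. Keep these participants in the denominator of the primary proportion, counted as non-responders if they were stopped for non-response or intolerance.
4. If the check is kept, describe safety results at week 12 and later as coming from those who passed it.
5. Report day-10 pharmacokinetic samples as absent for subset participants stopped earlier. No dose should be given to obtain them.

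The cost is protocol wording, one additional assessment for the few stopped early, and a response proportion that may be lower than the available-data figure. No extra participants are needed.

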### Safety and Efficacy

Primary and secondary end points for efficacy, as explained above, will be assessed on day 0, day 28, and 1 year after study drug cessation. The severity of any toxicity will be graded according to version 5.0 of the NCI CTCAE. Summaries of demographics, disposition, study drug exposure, protocol violations, and AEs will also be made.

An independent DSMB oversees trial conduct and participant safety. The DSMB reviewed safety data from the initial safety cohort (step 1) prior to progression to the expanded treatment phase (step 2). Ongoing safety oversight includes periodic review of AEs, protocol deviations, and overall study conduct. Study monitoring is conducted in accordance with Good Clinical Practice and NHRC ethical guidelines to ensure data quality, protocol adherence, and participant protection.

### Data Analysis

This study is designed as an exploratory phase 2 pilot trial; therefore, analyses will be primarily descriptive and longitudinal rather than inferential. All analyses will be conducted according to the intention-to-treat principle, including all participants who receive at least 1 dose of dovramilast, regardless of treatment duration, protocol deviations, or withdrawal.

Primary outcome analysis will focus on estimating the proportion of participants achieving a complete clinical response by day 10 of treatment, based on predefined clinical criteria encompassing skin, systemic, and neurological manifestations of ENL. This proportion will be summarized with descriptive statistics and corresponding confidence intervals to provide an estimate of response frequency and variability. Secondary outcomes will be assessed through longitudinal evaluation of ENL severity, pain, and neurological symptoms using validated instruments (EESS, Brief Pain Inventory, and Douleur Neuropathique 4). Changes in these measures over time will be summarized descriptively using means, medians, ranges, and graphical trend displays to assess patterns of improvement, remission, and recurrence during treatment and follow-up. The frequency and timing of ENL recurrences and the need for repeat dovramilast treatment cycles will be documented to characterize treatment durability. Exploratory laboratory and tissue outcomes derived from plasma and skin biopsy samples will be analyzed descriptively to evaluate trends in inflammatory, immunological, and histopathological markers over time.

In addition to clinical and exploratory outcomes, feasibility will be assessed as a key objective of this pilot study. Feasibility indicators include the ability to recruit and retain participants according to the protocol, adherence to study medication and follow-up schedules, completeness of clinical and patient-reported outcome data, and acceptability of study procedures. These feasibility measures, together with observed variability in outcomes and safety findings, will be used to inform decisions regarding the design, operational requirements, and scalability of a future adequately powered randomized controlled trial.

Given the pilot nature of the study, missing data will not be imputed; analyses will be based on available data, and the extent and reasons for missing data will be described and considered in interpretation.

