### Primary and Secondary Outcomes

The primary outcome is the proportion of participants achieving a complete clinical response by day 10 of dovramilast treatment. Complete clinical response is defined as a clinically meaningful improvement or resolution of ENL manifestations based on standardized clinical criteria rather than a binary presence or absence. This includes a reduction in the number, tenderness, and inflammation of ENL skin nodules, assessed clinically and supported by changes in the EESS score; resolution of ENL-associated fever based on clinical assessment and temperature recordings; and improvement or resolution of nerve pain and tenderness evaluated through neurological examination and validated pain assessment tools. Safety outcomes include the frequency and severity of AEs, graded according to the National Cancer Institute Common Terminology Criteria for Adverse Events (NCI CTCAE) version 5.0 [71], as well as laboratory abnormalities and neurological assessments. In addition, plasma and skin biopsy samples will be collected at predefined time points for exploratory evaluation of biological responses to dovramilast, including inflammatory and immunological markers relevant to ENL pathogenesis (such as circulating cytokines, acute-phase reactants, and immune cell–associated markers), and histopathological features of ENL lesions. These exploratory analyses will be descriptive and are intended to provide mechanistic insights into treatment response.

Secondary outcomes include the proportion of participants who achieve and maintain remission of ENL symptoms during treatment and for up to 12 months following cessation of the study drug. Longitudinal changes in disease severity, pain, and neurological symptoms will be assessed over time using validated instruments, including the EESS, Brief Pain Inventory, and Douleur Neuropathique 4 questionnaire. In addition, the frequency of ENL recurrence and the need for repeat dovramilast treatment cycles during the follow-up period will be documented.

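### The available-data rule leaves dosed participants without a day-10 status out of the primary denominator, which can bias the response proportion upward

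*Protocol article*

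**What the plan says.** All references are to the protocol article.

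- **Primary outcome** (Primary and Secondary Outcomes): "the proportion of participants achieving a complete clinical response by day 10 of dovramilast treatment".
- **Analysis population** (Data Analysis): intention-to-treat, "including all participants who receive at least 1 dose of dovramilast, regardless of treatment duration, protocol deviations, or withdrawal".
- **Missing data** (last paragraph of the same section): "missing data will not be imputed; analyses will be based on available data". The sentence goes on to say that "the extent and reasons for missing data will be described and considered in interpretation".
- **Stopping in step 1** (Step 1: Evaluation of the Immediate Effects): "If assessments during the 10-day initial treatment trial indicate poor safety or efficacy, participants may be removed from the treatment no later than day 10".
- **Continuation in step 2** (Step 2: Evaluation of the Long-Term Effects): "If patients tolerate the drug well and respond, they will continue to receive dovramilast for 12 weeks".
- **Follow-up after stopping**: the abstract's Methods and the Step 2 section both provide for 12 months of follow-up after the drug is stopped, monthly in step 2. The section on discontinuation and removal allows data collection to carry on after missed appointments, but does not require it.

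**The concern.** The two rules point in different directions for one kind of participant: someone who took at least one dose and has no recorded day-10 status. The population rule keeps that person in the primary analysis. The available-data rule takes them out. Counting them as a non-responder would itself be a simple imputation, which the text excludes.

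In many trials a few such cases would matter little. Here the design ties stopping before or at the primary time point to poor tolerability or poor response, so missing status is unlikely to be unrelated to outcome. Losing mostly failures from the denominator moves the proportion upward.

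There is no control arm in which the same distortion would show. The article intends the results to inform the end points and sample size of a later randomised trial (Sample Size and Justification; Future Directions), so an optimistic rate could be carried into that design.

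The longitudinal summaries of ENL severity (EESS), pain (Brief Pain Inventory, BPI) and neuropathic symptoms (Douleur Neuropathique 4, DN4) have a related weakness. If participants stopped by day 10 contribute few later values, the pooled curves rest mainly on day-10 responders and can fall through selection alone.

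**Working it through.** **What the plan gives.** Step 2 enrols up to 40 participants (Sample Size and Justification). The article states no expected response rate, no expected rate of early stopping and no confidence level, so there is no figure of the plan's own to reproduce.

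**Who is exposed.** Reading the passages together:

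1. *Stopped for lack of effect.* The Step 1 section rests removal on assessments made during the first 10 days. Such a participant has been assessed as not responding, so the status is observed and stays in the denominator under either rule.
2. *Stopped early for intolerance, or withdrew, with no day-10 assessment.* No status exists. The participant is in under the population rule and out under the available-data rule.
3. *Stopped for any reason, with status recorded at removal or at day 10.* The status is available and can be counted, so there is no bias.

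Only group 2 creates the problem. One detail makes a missing day-10 status more plausible: the Safety and Efficacy section lists efficacy assessments on day 0, on day 28 and at 1 year after cessation, without day 10. The Step 2 section does schedule a day-10 visit.

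**Size, for illustration.** Let N be the number dosed, x the documented responders and m the number without status.

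- All dosed, missing counted as non-response: x/N
- Available data: x/(N − m)
- Difference: x·m / [N(N − m)]
- Upper bound, if all missing had responded: (x + m)/N

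Assumed: N = 40, x = 24, and m = 0, 2, 6 or 8. Intervals are exact (Clopper-Pearson), two-sided 95%.

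| m | All dosed | Available data | Difference (points) | Upper bound |
|---|---|---|---|---|
| 0 | 24/40 = 60.0% (43.3 to 75.1) | 24/40 = 60.0% (43.3 to 75.1) | 0 | 60.0% |
| 2 | 60.0% | 24/38 = 63.2% (46.0 to 78.2) | 48/1520 = 3.2 | 26/40 = 65.0% |
| 6 | 60.0% | 24/34 = 70.6% (52.5 to 84.9) | 144/1360 = 10.6 | 30/40 = 75.0% |
| 8 | 60.0% | 24/32 = 75.0% (56.6 to 88.5) | 192/1280 = 15.0 | 32/40 = 80.0% |

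With a lower assumed response, x = 16, the all-dosed result is 16/40 = 40.0% (24.9 to 56.7). With m = 8 the available-data result is 16/32 = 50.0% (31.9 to 68.1), a difference of 10.0 points.

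The difference equals the bias only if the participants without status are in truth non-responders. If some of them responded, the true proportion lies between x/N and (x + m)/N.

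**The case against.** The strongest reply is that the article nowhere drops anyone. Removal is from treatment, not from the study or the analysis, and the population sentence covers early stopping and withdrawal explicitly. Not imputing is compatible with an all-dosed population: one rule defines who is included, the other says that values will not be invented. This stands. A reader might infer that the plan contradicts intention-to-treat, or that everyone removed by day 10 leaves the denominator; the text supports neither.

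The reply also points to follow-up. Twelve months of visits after the drug stops are already scheduled, with no stated exception for early stoppers. This also stands. A reader might infer that all later trends are inflated, but that is not established. The direction is not even certain: prednisolone and thalidomide are withheld only while the study drug is given, so removed participants may receive other ENL care, and pooling their later scores could lower the curve for reasons unrelated to dovramilast.

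Third, missing data will be described and considered, completeness of outcome data is a feasibility indicator, no hypothesis test is planned, and a separate analysis plan may give a denominator rule. These points lower the stakes, but describing missing data does not change the reported proportion or its interval. Nor is this only a detail left for later. The article fixes an available-data rule, and an analysis plan that counted missing status as non-response would depart from it.

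**Conclusion.** The point holds in a limited form. The article fixes two rules that are not reconciled for a dosed participant without a day-10 status, and the available-data rule, followed as written, takes that participant out of the primary denominator. Because stopping is tied to poor tolerability or response, the effect on the day-10 proportion can be upward.

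Under the assumption of 24 responders among 40 dosed, with 2 to 8 true non-responders lacking status, the overstatement is 3.2 to 15.0 percentage points. It is zero if the status of every removed participant is recorded and counted. The documents give no basis for choosing a value in that range, so the figures show sensitivity and do not predict the result. The consequence concerns estimation only, since no test or success threshold depends on the proportion.

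For the longitudinal scores, the conclusion is only that pooled curves after day 10 may reflect selection or other ENL treatment unless those stopped early are shown separately.

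**What to change.** 1. **Binary outcomes.** Replace the available-data sentence for these outcomes with a rule such as: all participants who received at least one dose form the denominator, and anyone without a documented complete response by day 10, for whatever reason, is counted as a non-responder. Report the available-data proportion as a sensitivity analysis.
2. **EESS, BPI and DN4.** State that the visits already scheduled after discontinuation apply equally to participants stopped by day 10. Show the number contributing at each visit, and display those who continued separately from those who stopped.

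The cost is a few sentences and one or two additional displays. No new visits are needed beyond those the Step 2 section provides. The Results section reports 15 participants recruited as of April 2026 and data collection continuing to September 2027, so the rule can be set before the step 2 results are known. The downside is that the stated response rate may be slightly less favourable.
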